# Meditation-based clinical study to determine the correlation of quantitative electroencephalogram (qEEG) and 24-hour EEG activity

**DOI:** 10.1097/MD.0000000000012557

**Published:** 2018-10-26

**Keywords:** 24-hour Holter monitor, activity ECG, meditation and mindfulness, qEEG, randomized controlled trial, stress and resource, study protocol

## Abstract

**Background::**

The heart continuously transmits information to the cerebrum during each pulse, and influences information processing such as perception, cognition, and emotion, which are processed in the cerebrum. This is the basis for the theory of oriental medicine widely used in psychiatric medicine and clinical practice, so-called Simjushinji (heart and brain) theory, that the heart controls the mind. The present study aims to analyze the correlation between heart and brain function by 24-hour active electrocardiogram and quantitative electroencephalogram (EEG) measurement under meditation.

**Methods::**

This randomized, controlled, assessor-blinded, 2-armed, parallel, multicenter clinical trial will analyze a total of 50 subjects, including 25 each for the test group and the active control group. Subjects will be randomly allocated to the test group (performing resource mindfulness) and the control group (performing stress mindfulness) in a 1:1 ratio. The clinical trial consists of 3 stages. The first and third stages are stable states. The second stage is divided into the test and active comparator groups. Quantitative EEG (qEEG) measurements at stages 1 and 3 will be recorded for 10 minutes; measurements at stage 2 will be recorded for 20 minutes with the eyes closed. The 24-hour Holter Monitoring and heart rate variability will be evaluated at each stage. Before the beginning of stage 3, subjects will complete the questionnaires. The primary outcome will be analyzed by independent *t* tests of both groups.

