### Sample size calculation

2.13

Based on the clinical trial study, the number of subjects was calculated as a minimum of 25 subjects each in the test and control groups, considering a 10% dropout rate. Based on previous studies,^[37,38]^ using the G∗power program, the total effect size was set at 1.0, and the total number of samples in the 90% confidence interval (CI) was set at 46 subjects. Considering a dropout rate of 10%, 50 participants must be recruited to collect sufficient data for statistical analysis and interpretation.

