### Statistical and analytical plans

2.14

To analyze the results of this clinical trial, the statistical software program SPSS 23.0 will be used to verify the homogeneity of each subject. The specific statistical analysis procedure is as follows. First, descriptive analysis (mean, frequency, SD) will be performed on the measured variables. Second, compared with baseline, nonparametric Wilcoxon sign^[39]^ and Wilcoxon matched-pair signed-ranks tests^[40]^ will be performed, according to the test group (RM) and the control group (SM). Third, a verification of differences will be performed between qEEG,^[19]^ 24-hour Holter monitoring,^[20]^ FFMQ-S,^[24]^ CSEI-SF,^[26]^ and K-PANAS,^[25]^ according to the baseline test and control groups. Finally, a nonparametric Spearman correlation analysis will be conducted on the basis of the quantitative brain wave (qEEG^[19]^), 24-hour Holter monitoring,^[20]^ FFMQ-S,^[24]^ CSEI-SF,^[26]^ and K-PANAS^[25]^ scales.

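### The abstract and section 2.14 disagree on the primary between-arm test, and no between-arm analysis adjusts for the stage-1 value

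*Protocol article*

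**What the plan says.** The article describes the comparison of the arms in two places.

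- **Abstract, Methods:** "The primary outcome will be analyzed by independent *t* tests of both groups". It does not name the variable or time point, or say whether the test is on the value after meditation or on the change.
- **Section 2.14, after descriptive statistics:**
  - Step 2: "Second, compared with baseline, nonparametric Wilcoxon sign" and matched-pair signed-ranks tests, which "will be performed, according to the test group (RM) and the control group (SM").
  - Step 3: "Third, a verification of differences will be performed between qEEG", Holter monitoring, FFMQ-S, CSEI-SF and K-PANAS, "according to the baseline test and control groups". No test is named.
  - Step 4: "Finally, a nonparametric Spearman correlation analysis will be conducted".

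The stage-1 data exist. The abstract says "Quantitative EEG (qEEG) measurements at stages 1 and 3 will be recorded for 10 minutes", and section 2.2 has HRV evaluated during each stage. Section 2.13 supplies the planning effect: "the total effect size was set at 1.0", with 46 subjects before dropout and 50 recruited.

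**The concern.** The primary result of a randomised trial is one contrast between arms. The abstract gives a parametric between-arm test for it. The section that should carry that test omits it and names only tests that answer other questions. A signed-rank test within RM and another within SM can be significant in one arm and not in the other without any evidence that the arms differ. The correlations do not estimate a treatment effect either. That leaves step 3, which has no test, no scale and unclear wording about baseline.

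An analyst could therefore choose between a t test on the later value and a t test on the change after seeing the data, and could cite the article for either. The two can differ materially in power. Separately, each participant supplies a same-day stage-1 recording before the meditations diverge, and no stated between-arm analysis uses it as a covariate.

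**Working it through.** **1. Which step tests RM against SM?**

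| Place | Test named | Compares RM with SM? |
|---|---|---|
| Abstract | independent t tests | yes; scale and time point not given |
| 2.14 step 2 | Wilcoxon tests against baseline | no, within arm |
| 2.14 step 3 | none | apparently; role of baseline unclear |
| 2.14 step 4 | Spearman | no |

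**2. Which does the sample size fit?** Inputs from section 2.13 are an effect size of 1.0 (read as Cohen's d) and 46 in total; the 1:1 ratio is from the abstract. Alpha is not stated. In a two-sample t test with noncentral t:

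- noncentrality = d·√(n₁n₂/(n₁+n₂)) = 1.0·√(23·23/46) = 3.391, with 44 df
- power at two-sided α = 0.05 is 0.912; with 22 per arm it is 0.8997, just under 0.90

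So 23 per arm, 46 in total, is exactly the requirement for 90% power. Two-sided 0.10 or one-sided 0.05, each with 95% power, also gives 46, so the article does not fix α. All three are two-sample t-test calculations, in line with the abstract rather than with step 2.

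**3. What the stage-1 covariate adds.** Let ρ be the correlation between the stage-1 value and the later value. The documents give none, so 0.3 to 0.7 is assumed. With equal SDs at both stages, variance relative to an unadjusted test on the later value is:

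- ANCOVA: 1 − ρ², so the effective d is d/√(1 − ρ²), with one df lost
- change score: 2(1 − ρ), so the effective d is d/√(2(1 − ρ))

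The planned case has d = 1.0 and 46 evaluable. The second case has d = 0.7 (an assumption, not in the documents) and 45 evaluable (50 × 0.9, split 22/23), with noncentrality 0.7·√(22·23/45) = 2.347. Two-sided α is 0.05 throughout.

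| ρ | 1 − ρ² | 2(1 − ρ) | d = 1.0: later value | d = 1.0: change | d = 1.0: ANCOVA | d = 0.7: later value | d = 0.7: change | d = 0.7: ANCOVA |
|---|---|---|---|---|---|---|---|---|
| 0.3 | 0.91 | 1.4 | 0.912 | 0.800 | 0.935 | 0.631 | 0.492 | 0.672 |
| 0.5 | 0.75 | 1.0 | 0.912 | 0.912 | 0.969 | 0.631 | 0.631 | 0.754 |
| 0.7 | 0.51 | 0.6 | 0.912 | 0.990 | 0.996 | 0.631 | 0.842 | 0.895 |

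Worked example: d = 1.0, ρ = 0.5 gives noncentrality 3.391/√0.75 = 3.916 on 43 df, and power 0.969.

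The unadjusted choice matters in both directions: change is worse than the later value below ρ = 0.5 and better above it. ANCOVA has the highest power in every row.

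**The case against.** The strongest reply is that this is incompleteness rather than contradiction. The Wilcoxon tests are within arm and the t test is between arms, so they can coexist. The abstract can be read as supplying the test that step 3 leaves out, and the sample size agrees with it. That is a fair reading and probably the intended one. But 2.14 presents itself as the specific procedure and still omits the primary test, and even the charitable reading leaves open whether the later value or the change is analysed.

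It is also fair that a condensed article may leave covariates and transformations to a fuller document. The absence of ANCOVA is therefore not in itself a wrong statement; it is an improvement that costs almost nothing while the text is being corrected.

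Several stronger readings are tempting, and the article does not support them:

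- *Step 3 compares the arms at baseline.* The wording allows it, but the questionnaires listed are exactly those repeated around stage 3, and the baseline-only instruments (such as HADS and PWI-SF) are absent. A comparison relative to baseline is at least as likely.
- *A between-arm rank test competes with the t test.* None is named.
- *Baseline balance will be tested for significance.* Section 2.14 speaks only of verifying homogeneity and states no test.
- *The unadjusted t test is biased.* Under randomisation it is not; chance imbalance is already reflected in its standard error.
- *Much power is lost as planned.* At d = 1.0 the gain is about 2 to 8 percentage points, because power is already about 0.91.
- *All outcomes need a log scale, or stage 2 is the primary time point.* The article says neither.

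**Conclusion.** The point holds in this form: the abstract's primary test is absent from 2.14, the tests that 2.14 does name leave the randomised contrast untested, and the analysed scale is open. This rests on the article's own text and needs no assumption.

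The precision argument is conditional. It assumes two-sided α of 0.05, that the effect size of 1.0 is Cohen's d, and ρ between 0.3 and 0.7. At the planned effect it is worth 0.912 to 0.935–0.996. It becomes substantial only if 1.0 is optimistic: at d = 0.7 with 45 evaluable, 0.631 to 0.672–0.895. The direction favours ANCOVA unless ρ is close to zero, where the lost degree of freedom is the only cost.

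**What to change.** Put one primary between-arm analysis, worded identically, in the abstract and section 2.14:

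- ANCOVA of the declared primary measure, at the stage the sponsor declares primary, on arm and the matching stage-1 value (same measure, same eye state), reporting the adjusted RM − SM difference with 95% CI. Section 2.10 lists many qEEG and HRV measures as primary, so the measure and stage must be named for this sentence to close the choice.
- A log scale only for strictly positive, skewed power measures; not for pNN50, for example, which can be zero. A rank-based ANCOVA as sensitivity analysis.
- Step 3 rewritten to name its test and say plainly how baseline enters.
- Within-arm Wilcoxon tests labelled descriptive.

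Section 2.9.2 places allocation at screening, before stage 1. Stage 1 is still a usable covariate because both arms are in the same resting condition until the meditation starts; the text should say so. For qEEG, the stage-1 eyes-closed segment lasts 5 minutes against 20 minutes at stage 2, so the match is in condition and not in length.

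The cost is one degree of freedom and a wording change. No further data or participants are needed. Recruitment was already open at publication, so the change should be made and dated before any comparison by arm is seen.

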**Discussion::**

Scientific studies based on clinical epistemology are expected to serve as a basis for sustainable medical services in the field of psychiatric medicine in Korea. HRV, blood pressure index, and biometric index in qEEG, as determined by 24-hour Holter monitoring, will complement quantitative biomarkers and be useful in various fields.

## Background

1

Brain and cardiovascular diseases contribute to the highest percentage of single-cause deaths (12.8%) worldwide. According to a 2017 report by the World Health Organization, 23.5 million people worldwide die of brain and cardiovascular diseases each year. In the West and in the Orient, a primary cause of these deaths was reported as mental stress.^[1,2]^ From the perspective of oriental medicine, this is very similar to the notion of the Chiljeong Sang—the concept that excessive emotions accumulate and a lack of coping resources causes stress, which then affects the body and wounds the internal organs,^[3,4]^ as written in the Dongui Bogam.^[5,6]^ In addition, the ubiquity and stress of excessive emotions cause damage beyond the internal organs, because it has the greatest impact and influence on the “heart,” which is the center of the body.^[7,8]^ This is similar to the context of the Shim Ju Shin Ji (heart and brain) theory, in which the “heart” (meaning mind) controls the “brain” (meaning cognition) in Oriental medicine. Physiologically, the heart continuously transmits information to the cerebrum during each heartbeat, which affects information processing such as perception, cognition, and emotion, which are managed in the cerebrum.^[9,10]^ The vagus nerve in the heart controls the activation of the parasympathetic nervous system. The vagus nerve transmits information regarding the heart, such as heart rate, heart rhythm, and blood pressure,^[11]^ to the cerebrum through an afferent pathway.^[12]^ Thus, information regarding the heart, originating from the vagus nerve, is integrated in the nucleus solitarius of the brainstem through the afferent nerve pathway. In the nucleus solitarius, integrated afferent information is transmitted to the cerebral cortex via the limbic thalamus, hypothalamus, and amygdala. Information transmitted to the cerebral cortex is subjected to information processing in the brain, and then travels to the heart and major organs via the efferent pathway.^[13]^ Based on the information returning from the cerebrum, the heart regulates the sympathetic and parasympathetic nervous system of the autonomic nervous system to maintain the homeostasis of the human body, and is involved in human emotion, cognition, and behavioral responses.^[14,15]^ Therefore, rather than separate interpretations of the brain and heart, the heart should be considered as an organ that interacts with the brain. In Donguibogam, the concept of “heart” is recognized as 3 things: mind, heart, and center.^[16]^

This study is undertaken to scientifically clarify the theory of Shinju (mind and heart) (body's behavior), in which the “mind” (meaning heart) is involved in the “brain” (meaning cognition).^[17]^ To do this, we will analyze the correlation between heart–brain function by using 24-hour active electrocardiogram (ECG) and quantitative electroencephalogram (EEG) during meditation. Specifically, subjects will be randomly assigned to 1 of 2 meditations recalling resources or stress situations, to observe the relationship between changes in 24-hour active ECG and quantified EEG. We will monitor the connectivity of the heart and brain by measuring the ECG and quantitative EEG (qEEG) through this study for 24-hour Holter monitoring during meditation, and will thus obtain regarding heart rate variability (HRV) and biomarkers for blood pressure and qEEG. In addition, clinical outcomes through mediation interventions can be used in various areas, including stress treatment, pain reduction, and cognitive awareness therapy for emotional instability. Furthermore, based on the epistemology, it is expected that the clear scientific identification of psycho-brain correlations will be the basis of sustainable medical services in the field of psychiatric medicine in Korea.

## Methods/design

2

This study protocol followed the Standard Protocol Items: Recommendations for Interventional Trials (SPIRIT) checklist, which enhanced the quality of the clinical trial.^[18]^

### Objectives

2.1

To scientifically identify the theory that the heart controls the mentality related with the brain, it is going to study on the correlation between the heart (mind and heart) and the brain (
[figure not shown]
) function by measuring the qEEG^[19]^ and activity ECG for 24 hours under meditation.

### Trial design and study setting

2.2

This clinical research will be conducted with subjects who provide voluntary consent and will be reviewed according to the inclusion or exclusion criteria of the clinical trial plan. Selected subjects will be assigned randomly into the test or active comparator group, according to precompleted random templates. The study design is as follows. This randomized, controlled, single-blinded, 2-armed, parallel, clinical trial will collect a total of 50 subjects, including 25 each for the test and active comparator groups. The subjects will be randomly allocated to a test group performing resource mindfulness (RM), and a control group performing stress mindfulness (SM), at a 1:1 ratio. The clinical trial consists of 3 stages, 20 minutes each (60 minutes total). The first and third stages are stable states. The second stage is divided into the test group and the active comparator group. The test group subjects will practice RM meditation and the active comparator group subjects will practice SM meditation. RM or SM meditation guide scripts will follow the M&L Psychotherapy Manual and the meditation guide will be directed by a professional practitioner trained by the M&L psychotherapist course. At stages 1 and 3, qEEG measurements will be taken for 10 minutes (5 minutes with eyes open and 5 minutes with eyes closed) from 5 minutes after the beginning of the stage. In the second stage, the qEEG measurements will be taken for 20 minutes, with eyes closed. The 24-hour Holter monitoring^[20]^ will be performed through stages 1, 2, and 3; HRV will be evaluated during each stage. The blood pressure and pulse will be measured before and after the second stage. All processes related with clinical trial including plans for collecting, assessing, reporting, and managing solicited and spontaneously reported adverse events and other unintended effects of trial interventions or trial conduct will be monitored and modified primarily by researcher director and peer researchers to ensure participants’ safety and research design's accuracy. A diagram and the time schedule of this study are shown in Table 1 and Fig. 1.

**Table 1 T1:**
[figure not shown]
Time schedule of study.

**Figure 1 F1:**
[figure not shown]
Summary of clinical trial design.

### Recruitment

2.3

Department of Neuropsychiatry of Korean Medicine & Inam Neuroscience Research Center, Wonkwang University Sanbon Hospital in Korea will recruit outpatients in the clinical practice setting. Clinical trial information will be posted on the bulletin board of each hospital and university, in online advertisements.

### Eligibility criteria: inclusion criteria

2.4

1.Age: male and female individuals, age: 20 to 45 years2.Individuals who do not consume excessive amounts of tobacco, tea, and coffee; who eat regularly; and who have a normal sleep pattern3.Individuals who exhibit right-handedness4.Individuals who voluntarily participate in the study, as indicated by their written consent (or that of a legal representative when the individual has limited ability to agree, but can still express willingness to participate)

### Eligibility criteria: exclusion criteria

2.5

1.Individuals who demonstrate arrhythmia on EKG, or whose pulse rate per minute is outside of the range of 50 to 1002.Individuals who have a severe physical illness or are medically unstable (as determined by the clinical trial conductor or another medical expert)3.Individuals who have a congenital illness, psychological illness, central nervous problem, peripheral nervous problem, endocrinal illness, immunological disease, basal heart disease, liver disease, or renal disease4.Individuals who have a neurological illness (eg, head trauma) or psychological history (eg, major depressive disorder, anxiety disorder, bipolar disorder, or schizophrenia)5.Individuals with an intracardiac pacemaker inserted, or with a device that stimulates the brain, a ventricular peritoneal short circuit, or other artificial device inserted into the head6.Individuals who take medicines that may affect the autonomic nervous system within 1 week before enrollment in the clinical trial (opiates, stimulants, tricyclic antidepressants, benzodiazepines, cardiac drugs such as beta-blockers, or renin-angiotensin-aldosterone system blockers such as angiotensin-converting enzyme inhibitors and angiotensin receptor blockers)7.Individuals who smoke, drink alcohol, or ingest caffeine-containing products, within less than 2 hours before the clinical trial (eg, coffee, coffee milk, black tea, green tea, cocoa, colas/sodas, chocolate, caffeine-containing energy drinks)8.Individuals who are pregnant or breast feeding9.Individuals who participated in another clinical study within the prior 1 month or who are currently participating in other clinical studies10.Individuals who exhibit difficultly participating in this study, as judged by the investigator

### Subject withdrawal criteria

2.6

1.Violation of the inclusion criteria or fulfillment of the exclusion criteria2.Serious adverse events that impede trial continuation3.Withdrawal of consent by the subject or a legal representative4.Do not receive 3 consecutive mindfulness meditation sessions5.Violation of the clinical trial protocol by the investigator or the subject6.Use of medications or treatments that can affect the results for clinical trial7.Inappropriate progress as judged by the investigator

### Randomization and allocation concealment

2.7

A randomization table will be created by an independent statistician using the balanced block.

#### Randomization with Excel 2016

2.7.1

The randomization number allocated according to the assigned tables generated will be managed by the clinical trial manager and sent to each hospital. Consent will be obtained by a Korean Medicine doctor. If the participant voluntarily signs informed consent and meets the inclusion criteria, the clinical research coordinator (CRC) will sequentially allocate the participant to the treatment or control group according to the random number and record the subject identification code on the case recording sheet and the assignment table.

### Blinding: single blind

2.8

Because of the study design, practitioners cannot be blinded. Only the participants will be blind. The assessor will be instructed to refrain from talking about the treatment to maintain blinding.

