#### Test group intervention: resource mindfulness group

2.9.5

Resource mindfulness is to experience a safe and comfortable state by recalling the positive nourishment (resource) inside subject within the mindfulness state

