#### Active comparator group intervention: stress mindfulness group

2.9.6

Stress mindfulness is to experience emotions, feelings, memories, thoughts, and so on occurring within me when I recall a difficult situation inducing stress in the state of mindfulness.

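### Section 2.8 rests the single blind on the participants, but they cannot be blind to the meditation they perform, so the three self-report scales are unblinded

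*Protocol article*

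**What the plan says.** Section 2.8 of the protocol article is the only place that describes the blind: "Because of the study design, practitioners cannot be blinded. Only the participants will be blind". It adds one measure to protect it: "The assessor will be instructed to refrain from talking about the treatment to maintain blinding".

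Two other places label the design. The abstract has "This randomized, controlled, assessor-blinded, 2-armed, parallel, multicenter clinical trial", while Section 2.2 has "This randomized, controlled, single-blinded, 2-armed, parallel, clinical trial will collect a total of 50 subjects".

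The arms are defined by the mental content of stage 2. In the test arm (Section 2.9.5) the participant is to "experience a safe and comfortable state by recalling the positive nourishment (resource) inside subject within the mindfulness state". For the comparator, Section 2.9.6 says: "Stress mindfulness is to experience emotions, feelings, memories, thoughts, and so on occurring within me when I recall a difficult situation inducing stress". In both arms a trained guide follows a script from the same psychotherapy manual (Sections 2.2 and 2.9.4).

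FFMQ-S, K-PANAS and CSEI-SF are completed before the trial and again after the meditation (Sections 2.9.3 and 2.10.3). Section 2.14 puts them in the group comparison, which begins "Third, a verification of differences will be performed between qEEG" and goes on to list Holter monitoring and the three scales. The same five sets of measures then enter a Spearman correlation analysis.

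**The concern.** The only party that Section 2.8 calls blind is the party that has to carry out the differing instruction. The reason the section gives for not blinding practitioners, the study design, applies equally to participants: they hear the same script and then perform it.

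This matters most where the participant is also the rater. Affect (K-PANAS), emotion (CSEI-SF) and mindfulness (FFMQ-S) are reported shortly after a session that was openly pleasant or openly difficult in content. A difference between arms may partly reflect what participants think they are expected to report. A reader told that the trial is participant-blind would give such a difference more weight than it can bear. The same applies to correlations of these scales with qEEG or heart rate variability.

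**Working it through.** There is no figure in the plan to reproduce. The check is to set the sections side by side.

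1. **Who is said to be blind.** Section 2.8: participants only. Section 2.2: single-blinded, with no party named. Abstract: the assessor. Section 2.2 fits Section 2.8; the abstract names a different party.

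2. **What separates the arms.** Stages 1 and 3 are resting states in both arms. Stage 2 has the same length, recording and type of guide in both. What differs is the content recalled (Section 2.9.5 against Section 2.9.6).

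3. **Can that content be hidden from the participant?** No. Recalling a resource or a stressful situation on instruction requires knowing the instruction. What could be hidden is the content of the other arm, the hypothesis, or which arm is the test arm. Section 2.8 names none of these as the object of the blind.

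4. **Does the stated safeguard help?** The assessor's silence about treatment may avoid revealing the other arm or the expected direction. It cannot hide the task the participant has just done.

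5. **When the scales are filled in.** The abstract and Section 2.10.3 place them just before stage 3; Section 2.9.3 places them at the third stage. On either account they follow stage 2, so the rater knows the task.

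6. **How much of the analysis is touched.** Section 2.14 lists five sets of measures: qEEG, Holter, FFMQ-S, CSEI-SF and K-PANAS.
   - Group comparison: 3 of the 5 are self-report.
   - Correlations, assuming every pair of sets is examined (the article does not list the pairs): 5 × 4 / 2 = 10 pairs. Only qEEG–Holter contains no self-report, so 10 − 1 = 9 pairs contain at least one unblinded scale.
   - Participants: all 50 (25 per arm), since each performs one of the two tasks.

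7. **What is less exposed.** qEEG and Holter signals are recorded by instrument. One step involves judgement: Section 2.10.1 has an expert remove EEG artifacts by hand. Whether that expert is masked depends on which blinding statement governs, so the conflict in step 1 has a practical consequence.

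**The case against.** The strongest reply is that single blind can reasonably mean masking to the hypothesis or to arm status. Both arms receive a scripted, active mindfulness session from a trained guide, and someone who hears one script need not know the other or which is favoured. This stands as a possibility. A reader might infer from Section 2.8 that no participant masking of any kind can exist; the document does not support that. But partial masking is not what the section states, and it would still leave affect and emotion rated by someone who knows the task.

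Other stronger readings also fail:

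- *The heart–brain result is compromised.* The stated objective (Section 2.1) is the relation between qEEG and ambulatory ECG, and that correlation uses no self-report. Only analyses involving the three scales carry the problem.
- *The abstract claims a participant blind.* It does not; it names the assessor. What is needed there is reconciliation.
- *The subject-facing material reveals the arms or lacks neutral labels.* The consent text and advertisements are not shown, so this cannot be known.
- *Comparator participants are told to feel stress.* Section 2.9.6 asks them to experience whatever arises when a difficult situation is recalled, which is a weaker demand.
- *The questionnaires will be used to claim efficacy.* No section makes such a claim.

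It is also fair that unblinded self-report is inherent in comparing two meditation contents. That makes it a limitation to state; it does not make the participant-blind statement accurate. A fuller protocol could not alter this, because no procedure can keep participants unaware of what they are asked to recall.

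**Conclusion.** The point holds for blinding to the intervention received. Section 2.8 states a property that the arm definitions rule out; at most, participants are masked to the hypothesis or to which arm is the test arm. Between-arm differences and correlations involving FFMQ-S, K-PANAS and CSEI-SF are therefore unblinded and open to demand effects in all 50 participants. The size and direction of any bias cannot be derived from the document. The conclusion rests only on the arm definitions and on the scales being completed after stage 2.

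The sample size and the qEEG–Holter analysis are not affected. The correction should be made because it limits what may be concluded from the questionnaires.

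**What to change.** **Section 2.8.** Replace the participant-blind statement with something like: *participants know their meditation task; they are masked at most to the study hypothesis and to which arm is the test arm.* Claim that partial masking only if it is actually practised.

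**Abstract and Section 2.2.** Reconcile the two labels with the corrected Section 2.8, saying who is masked and to what. If assessor masking is intended, say so in Section 2.8 as well, including whether it covers the expert who removes EEG artifacts.

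**Section 2.14.** State that group differences and correlations involving FFMQ-S, K-PANAS and CSEI-SF are unblinded and supportive only, and that the main conclusions rest on qEEG and heart rate variability. K-PANAS and CSEI-SF may be read as a check that stage 2 induced the intended state; this is one reasonable framing, not the only one.

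**Cost.** A few sentences, with no change to procedures, sample size or the instrument-based analysis. The price is a less favourable description of blinding and weaker claims from the questionnaires.
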